## Abstract

**Background:**

The rapid increase in childhood obesity is a serious public health problem, and has led to the development of many interventions. However, no intervention has emphasized whole grains as a strategy to manage childhood obesity. Therefore, this article describes the protocol of a 12-week multi-component, family-based intervention on whole grain, using a healthy balanced diet for managing childhood obesity.

**Methods:**

The GReat-Child trial utilize a quasi-experimental method in which two schools in Kuala Lumpur are assigned to intervention and control groups. The eligibility criteria are overweight/obese children, aged 9 through 11 years, who has no serious co-morbidities. The children who report consuming whole-grain foods in their 3-day diet-recall during the screening will be excluded. The study sample is characterized by anthropometric measurements (weight, height, percentage of body fat and waist circumference), whole grain and nutrient intakes (3-day 24-h diet recalls), and their knowledge, attitudes and practices towards whole grain. The 12-week intervention is comprised of three components addressing behaviour, personal and environmental factors, based on social cognitive theory: (1) individual diet counselling for the parents; (2) six 30-min nutrition education classes and (3) school delivery of whole-grain foods; The control school does not receive any interventions, however, for ethical purposes, a health talk is conducted after the entire GReat-Child Trial is completed.

**Conclusion:**

The GReat-Child trial represents a novel approach to examining the effectiveness of the intervention of whole grain in a healthy balanced diet on managing childhood obesity. We anticipate that this trial will reveal not only whether whole grain intervention will be effective in managing childhood obesity, but also provide greater insights into the acceptance of whole grain among Malaysian children.

## Background

Childhood obesity is a chronic disorder, which is defined as excessive body fat deposition that presents an adverse effect on health (Fernandez-Sanchez et al. 2011). It poses a global public health threat and has risen to an alarming level throughout the world (Theodore et al. 2009). The long-term persistence of obesity in childhood leads to several chronic diseases, such as hyperlipidaemia, hypertension and hyperinsulinemia (Linberg et al. 2012). Apart from the above-mentioned chronic diseases, the findings from one study have indicated a significant increase in the psychosocial consequences of childhood obesity (Centers for Disease Control and Prevention 2009). For example, children who are obese have a negative body image, which leads to lower self-esteem, and reflects negatively on their academic and social progress (Ben-Sefer et al. 2009). The complications caused by childhood obesity are severe, and could continue to affect the health of a child, even in adulthood (Centers for Disease Control and Prevention 2009).

In recent years, the rates of childhood obesity in Malaysia have been rising dramatically (IPH 2011), similar to the global patterns (Kipping et al. 2006). This rising problem of childhood obesity has led to the development of intervention programs against obesity starting in early life. Successful childhood obesity intervention may be useful as a secondary prevention, decreasing the complications of childhood obesity on co-morbidities later in life (Reilly 2006). The essential elements of any intervention are likely to include dietary modifications and nutritional education (Kirk et al. 2005). Several childhood obesity interventions testing nutritional education and diet modification have been initiated in several countries, such as the United States (Davison et al. 2013), Canada (Anand et al. 2007), the United Kingdom (James et al. 2007), New Zealand (Graham et al. 2008), Singapore (Gupta et al. 2010) and Malaysia (Sharifah et al. 2011); however, none of these interventions emphasized the provision of whole grain to manage childhood obesity.

A recent meta-analysis concluded that adults consuming more than three servings of whole grain had a consistently lower risk of obesity (Ye et al. 2012). Additionally, both epidemiological (McKeown et al. 2009) and randomized intervention trials (Maki et al. 2010) conducted among adults from the US have demonstrated that the abdominal fat mass was reduced on a whole-grain diet, compared to refined grain, an effect which has not been reported for fruits and vegetables (McKeown et al. 2009). In children, the correlation between the consumption of whole grain and health benefits has been less explored. However, previous cross-sectional studies from the US have reported that the consumption of whole grain can improve the diet quality (Bellisle et al. 2014) and body mass index (BMI) z-scores (Choumenkovitch et al. 2012) among children.

In spite of the positive health benefits and dietary recommendations, the national dietary intake data from the US (Harnack et al. 2003), France (Bellisle et al. 2014), Malaysia (Norimah et al. 2015) and Singapore (Health Promotion Board Singapore 2010) have demonstrated that whole grain consumption is considerably low. In Kuala Lumpur, a recent local study revealed that the practice of consuming whole grain was low there too, with less than 10 % reported daily consumption of whole grain (Koo et al. 2015a). A quasi-experimental trial has been conducted in the US, aiming to increase the whole grain consumption among children (Burgess-Champouxt et al. 2007). However, this quasi-experimental trial did not investigate the association of whole grain intake with anthropometric measurements, which helps in managing childhood obesity (Burgess-Champouxt et al. 2007).

Home environment and family has been widely recognized as one of the influences in child’ seating behaviours and dietary intake (Golan 2006). Parental involvement is a critical and feasible component in an intervention which raises positive dietary behavioural changes for children (Perry et al. 1998). A meta-analysis that involved 42 weight-related health interventions demonstrated that parental involvement in the interventions was more effective in managing childhood obesity (Niemeier et al. 2012). Another review revealed that the majority of studies reported a positive effect of home-based interventions which included family members in combating childhood obesity (Knowlden and Sharma 2012). The overall effectiveness and sustainability of an intervention program could be improved by identifying parent-friendly strategies that promote active, sustained participation (Burgess-Champouxt et al. 2007).

The purpose of this present article is to describe the rationale and design of a multi-component, family-based intervention on whole grain combined with a healthy balanced diet to manage childhood obesity, utilizing a quasi-experimental trial design: the GReat-Child Trial. To the best of our knowledge, this is the first trial that has focused on whole grain to manage childhood obesity. It was hypothesized that, in the school post-intervention comparison, the children in the intervention school would have: (1) improved anthropometric measurements by increasing their wholegrain consumption; (2) improved knowledge, attitudes and practices towards whole grain; (3) improved overall nutrient intake and (4) increased availability of whole-grain foods at home.

## Methods

### Trial design and sample size calculation

The flow diagram of the trial design is shown in Fig. 1, and a list of government primary schools in Kuala Lumpur is obtained from the Kuala Lumpur Federal Territory Education Department. Kuala Lumpur is the federal capital and most populous city in Malaysia, and consists of three zones: Sentul, Keramat and Bangsar-Pudu. Two primary schools are recruited from a randomly selected zone to participate in the present trial. Schools with similar social and demographic characteristics are assigned to the intervention and control conditions on a non-randomized basis, in order to make sure the intervention and control groups were completely independent, sufficiently far apart and without any effect on each other (McMillan 2007). The inclusion criteria are: (1) apparently healthy Malaysian school children aged 9–11 years or studying in years 4 and 5; (2) children who are overweight or obese (BMI for age > +1 SD, relative to the WHO reference data) (World Health Organisation (WHO) 2007); (3) able to read, write and understand Malay; and (4) at least one parent who perceives that their child has a weight problem, and who is willing to attend the individual diet counselling. The perception of childhood obesity is considered important in order to recruit only participants who are receptive to the intervention, and who are sufficiently motivated to complete all of the intervention sessions (Wafa et al. 2011). Children are excluded: (1) if they have a serious co-morbidity requiring treatment or on gluten-free diet and (2) if any of their 3-day 24-h diet-recall during screening indicate that they had consumed whole-grain food in the previous week. The study protocol was reviewed and approved by the Universiti Kebangsaan Malaysia Research Ethics Committee, and permission to carry out the data collection was granted by the Ministry of Education, Malaysia and the Kuala Lumpur Federal Territory Education Department. Parental consent is obtained for all children prior to participation, while verbal assent is also obtained from the children before the study begins.

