**Fig. 1 Fig1:**
[figure not shown]
Flow diagram of the GReat-Child trial design

The standard deviation (SD) of the BMI-for-age z-score obtained from a previous study (Madsen et al. 2009) is taken into consideration for the sample size calculation of this present trial. With the SD of the BMI z-score equal to 0.10, giving a detectable difference of 0.08, a sample size of around 25 children per group at 12 weeks would give 80 % power at the 0.05 significance level. The sample size was estimated using the following equation (Naing 2009):$$ {\rm n} =[2 \upsigma^2/\Updelta^2]  ({\rm Z}_{\upalpha}+{\rm Z}_{\upbeta})$$where n = estimated sample size, σ = standard deviation for BMI-score from previous study = 0.10, ∆ = detectable difference = 0.08, Z_α_ = significance level for two-sided test = 1.96, Z_β_ = 80 % power of study = 0.84.

The sample size required for this study is 25 per group. While taking into account a non-response rate of 50 %, the required sample size for each group is increased to 38; therefore, the total number of children needed is 76. Any children who wish to dropout are allowed to do so, with the reasons being noted and analysed.

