### Statistical analyses

Statistical analysis is conducted using the SPSS version 22.0 (IBM SPSS Statistics 2014). Data are entered, cleaned and checked before data analyses. Each variable is examined for normality distribution using the Kolmogorov–Smirnov test. Categorical data will be presented as number and percentage. Continuous data will be presented as mean and standard deviation or median and range. Association between categorical variables items and the two groups (intervention and control groups) are determined using Chi square test. The differences between intervention and control group across anthropometric measurements, pedometer step counts, whole grain and dietary intakes, as well as scores of KAP towards whole grain are determined using independent *T* test and Mann–Whitney U test. Analysis of covariance for repeated measures (ANCOVA) is performed to determine the intervention effects, such as the differences in anthropometric measurements, pedometer step counts, whole grain and dietary intakes, as well as scores of KAP towards whole grain between the intervention and control groups. Three models were examined, including (1) within group difference based on time; (2) between group differences regardless of time and (3) between group differences with regard to time. Baseline variables are considered as confounders in each models in order to prevent bias. Model assumptions including normality of the residuals, homogeneity of variance, compound symmetry and homogeneity of regression will be verified. P-value of less than 0.05 for a two-sided test is considered statistically significant.

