## Conclusion

In conclusion, the GReat-Child Trial is the first multi-component, family-based intervention focussing on whole-grain consumption with healthy balanced diet for managing childhood obesity. The novel approach to obesity intervention, which is based on systematic reviews and clinical management guidelines for childhood obesity, provides evidence of the efficacy of whole grain intervention in managing childhood obesity. Furthermore, it will provide better understanding of the acceptance of whole grain among Malaysian children in particular and among Asian children in general.

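### One non-randomised school per arm is powered and analysed as if children were independent, so the stated 5 % level and 80 % power hold only if the within-school correlation is zero, and a school-specific change over time cannot be told apart from the intervention effect

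*Protocol article*

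**What the plan says.** Three parts of the protocol article fix the point.

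- **Design.** The abstract says that "two schools in Kuala Lumpur are assigned to intervention and control groups". Under Trial design and sample size calculation: "Two primary schools are recruited from a randomly selected zone to participate in the present trial". On how the arms were formed, that section adds: "Schools with similar social and demographic characteristics are assigned to the intervention and control conditions on a non-randomized basis". So there are two schools, one per arm, and the school is the unit of assignment. The classes and the daily whole-grain food are also delivered at school to the intervention children together.
- **Sample size.** The same section takes an SD of 0.10 and a difference of 0.08 for the BMI z-score, and concludes that "a sample size of around 25 children per group at 12 weeks would give 80 % power at the 0.05 significance level". The formula is the one for two independent means, with "significance level for two-sided test = 1.96". No ICC or design effect appears. The target is then raised to 38 per group, 76 in total.
- **Analysis.** Statistical analyses names an independent t test, a Mann-Whitney test and a repeated-measures ANCOVA on children, with no school term. It adds: "Baseline variables are considered as confounders in each models in order to prevent bias".

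The Conclusion then says that the approach "provides evidence of the efficacy of whole grain intervention in managing childhood obesity".

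**The concern.** Children in one school share surroundings, staff and, here, the delivery of the intervention, so their outcomes may be correlated. A child-level test uses only the spread among children within each school to judge the difference between the arms. It leaves out the variation that would make two schools differ even without an intervention. If that variation is not zero, the standard error is too small, the confidence interval too narrow and the P-value too low.

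With one school per arm this cannot be put right from the trial's own data. School and arm are the same variable, so no mixed model or cluster-robust variance can estimate the missing component. What is at stake is the reading of the primary result: a significant difference in BMI z-score change could reflect the intervention, or two schools that happened to move differently over the same months.

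**Working it through.** **Inputs from the article.** SD 0.10, difference 0.08, two-sided z = 1.96, power z = 0.84, 25 per group required, 38 per group recruited, one school per arm.

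**Assumed.** ICC of 0.01, 0.02 and 0.05 for the analysed outcome (none is given), with 0.10 taken as the total SD.

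**1. Reproduce the stated size.** With the squared z-term, n = 2 × 0.10² / 0.08² × (1.96 + 0.84)² = 24.5, rounded up to 25. (The formula is printed without the square and would then give 8.75. That is a separate matter, since 25 plainly comes from the squared form.) The recruitment target is 25 × 1.5 = 37.5, rounded up to 38. The figure of 25 therefore reproduces exactly with no clustering term, that is, at ICC = 0.

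**2. Degrees of freedom for school.** Two schools minus two arm means = 0. Between-school variance cannot be estimated.

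**3. Type I error of the child-level test.** With m children per school, the true variance of the difference is proportional to 1 + (m − 1)ICC. The child-level standard error estimates only the within-school part, proportional to 1 − ICC. The ratio is

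R = [1 + (m − 1)ICC] / (1 − ICC) = 1 + m × ICC / (1 − ICC).

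The true two-sided error is 2Φ(−1.96/√R). Example: m = 25, ICC 0.05 gives R = 1 + 25 × 0.05/0.95 = 2.32, √R = 1.52, and an error of 19.8 %. A t reference distribution gives 19.3 %.

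**4. Power of a test that holds its 5 % level, with the ICC treated as known.** With DE = 1 + (m − 1)ICC, power = Φ(0.08 / [0.10 × √(2 × DE/m)] − 1.96). Example: m = 25, ICC 0.01 gives DE = 1.24, √(2 × 1.24/25) = 0.315, 0.8/0.315 = 2.54, and power Φ(0.58) = 72 %.

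| m per school | ICC | DE | √R | True type I error (t / normal) | Power, ICC known |
|---|---|---|---|---|---|
| 25 | 0 | 1.00 | 1.00 | 5 % | 81 % |
| 25 | 0.01 | 1.24 | 1.12 | 7.9 / 8.0 % | 72 % |
| 25 | 0.02 | 1.48 | 1.23 | 10.8 / 11.1 % | 64 % |
| 25 | 0.05 | 2.20 | 1.52 | 19.3 / 19.8 % | 48 % |
| 38 | 0 | 1.00 | 1.00 | 5 % | 94 % |
| 38 | 0.01 | 1.37 | 1.18 | 9.5 / 9.6 % | 85 % |
| 38 | 0.02 | 1.74 | 1.33 | 13.9 / 14.1 % | 75 % |
| 38 | 0.05 | 2.85 | 1.73 | 25.4 / 25.8 % | 54 % |

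Here 25 is the number the calculation requires and 38 is the recruitment target with no losses. More children per school raises power but makes the type I error of the child-level test worse.

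**5. Ceiling on power.** With one school per arm and a known ICC, the number of children per arm for 80 % power is 24.5(1 − ICC)/(1 − 24.5 × ICC). This is about 33 at ICC 0.01, 48 at 0.02 and 90 at 0.03. Above ICC = 1/24.5 = 0.041, no number of children in two schools is enough.

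**The case against.** Several points on the other side are fair.

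- **Baseline data.** A reader might infer that any difference between the schools is indistinguishable from the intervention effect. The documents do not support that. There is a baseline assessment, baseline variables enter every model, and one of the three models is the between-group difference with regard to time. Together these address stable differences in outcome level. What stays confounded is a differential change between the schools over the follow-up. A plain t test or Mann-Whitney test on follow-up values would still be exposed to level differences as well.
- **The ICC is unknown.** The relevant ICC is that of the baseline-adjusted outcome, and it may be small. That stands. The direction is clear for any positive ICC, but the size is not. At 38 per school and ICC 0.01, power is still about 85 %, so it would be wrong to say that power falls below 80 % in every case.
- **The article discloses the design and hedges on efficacy.** It calls itself quasi-experimental and non-randomised, chooses similar schools that are well apart, and the Discussion says efficacy is not yet conclusive. A reader might take the Conclusion's sentence as a claimed result, but no result is reported, so this is mainly a matter of wording. The hedge, however, rests only on the study being unfinished. Disclosing non-randomisation does not disclose that P-values leave out between-school variation.
- **An analysis plan could handle it.** It could not handle the core of it. The number of schools, the formula and the tests are fixed in the article, and no plan can estimate between-school variance from one school per arm.

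**Conclusion.** The point holds in this form. Sample size and analysis both assume independent children although the school is the unit of assignment and each arm has one. The nominal 5 % level and the 80 % power at 25 per group are therefore conditional on ICC = 0. Over assumed ICCs of 0.01 to 0.05, the true type I error runs from about 8 to 20 % at 25 per school and from about 10 to 26 % at 38. Power runs from about 72 down to 48 %, and from about 85 down to 54 %. These figures rest on the assumed ICCs and on 0.10 as the total SD. The confounding of the intervention with a school-specific change over time rests on no assumption about the ICC: it follows from having one school per arm. Child-level baseline adjustment cannot remove it, so the article's statement about preventing bias goes too far.

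**What to change.** 1. **Trial design and sample size calculation.** State that 80 % power at 25 per group assumes ICC = 0. Restate power with the design effect at both 25 and 38 per school for ICC 0.01, 0.02 and 0.05.
2. **Statistical analyses.** State that the school is the unit of assignment with one per arm, and that child-level P-values and confidence intervals are conditional on these two schools. Report the primary BMI z-score difference with its 95 % CI recomputed at ICC 0.01, 0.02 and 0.05, multiplying the child-level standard error by √[1 + m × ICC/(1 − ICC)]. The familiar multiplier √[1 + (m − 1)ICC] is slightly too small here, because the child-level standard error already lacks the between-school part (variance ratio 2.20 against 2.32 at m = 25, ICC 0.05).
3. **Same section, wording on confounders.** Say that adjustment reduces child-level baseline imbalance, not that it prevents bias.
4. **Conclusion.** Describe the result as a difference between two schools, not as evidence of efficacy, and give the design as a reason for caution alongside the study being ongoing.

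The cost is a paragraph in two sections, one sensitivity table, wider intervals and a weaker claim. No schools are added. These changes qualify the conclusion and do not repair the design: separating school from intervention would take several schools per arm.

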**Fig. 1 Fig1:**
[figure not shown]
Flow diagram of the GReat-Child trial design

The standard deviation (SD) of the BMI-for-age z-score obtained from a previous study (Madsen et al. 2009) is taken into consideration for the sample size calculation of this present trial. With the SD of the BMI z-score equal to 0.10, giving a detectable difference of 0.08, a sample size of around 25 children per group at 12 weeks would give 80 % power at the 0.05 significance level. The sample size was estimated using the following equation (Naing 2009):$$ {\rm n} =[2 \upsigma^2/\Updelta^2]  ({\rm Z}_{\upalpha}+{\rm Z}_{\upbeta})$$where n = estimated sample size, σ = standard deviation for BMI-score from previous study = 0.10, ∆ = detectable difference = 0.08, Z_α_ = significance level for two-sided test = 1.96, Z_β_ = 80 % power of study = 0.84.

The sample size required for this study is 25 per group. While taking into account a non-response rate of 50 %, the required sample size for each group is increased to 38; therefore, the total number of children needed is 76. Any children who wish to dropout are allowed to do so, with the reasons being noted and analysed.

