### Anthropometric measurement outcomes

The primary outcome measured is the BMI-for-age z-score, which is compared between the intervention and control groups. The body weight and height of each child are measured twice, according to standard procedures, using a calibrated Tanita digital scale Model SC-330 (Tanita Co., Tokyo, Japan) and SECA Bodymeter 217 (SECA GmbH & Co., Hamburg, Germany), respectively. The measurements are recorded to the nearest 0.1 kg and 0.1 cm, respectively. The body mass index (BMI) of each child is calculated by dividing the measured weight (kg) by the square of the height (m). The World Health Organization (WHO) BMI-for-age growth reference for children aged 5–19 years old (30) served as the standard reference for determining the nutritional status of the children. The z-scores for BMI-for-age (BAZ) are determined using the software WHO AnthroPlus version 1.0.3, and children are classified into overweight (BAZ +1SD to +2SD) and obese (BAZ > +2SD) categories. The percentage of body fat is measured twice by bioelectrical impedance using the TANITA digital scale Model 300GS (Tanita Co., Tokyo, Japan) and nearest to 0.1 %. The children stood bare footed on the scale, after the electrode of the scale is cleaned to remove any debris. Any objects that could interfere with the readings are removed from their pockets before the measurements are taken.

Waist circumferences (WC) of the children are measured twice, according to the standardised protocol by the National Health and Nutrition Examination Survey (NHANES), which assessed the WC just above the right iliac crest at the mid-axillary line (Centers for Disease Control and Prevention National Health and Nutrition Examination Survey 2000). The WC is measured to the nearest 0.1 cm by using a Lufkin tape model W606PM (Apex Tool Group, Maryland, USA). Finally, the reported values of the body weight, height, percentage of body fat and WC are the average values from the two readings taken.

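### The 80 % power rests on an SD of 0.10 for the BMI z-score, which is implausible for children recruited anywhere above +1, so the power is not established for the primary outcome as defined

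*Protocol article*

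**What the plan says.** Under Trial design and sample size calculation, the protocol article describes its variance input as "The standard deviation (SD) of the BMI-for-age z-score obtained from a previous study" and then writes "With the SD of the BMI z-score equal to 0.10, giving a detectable difference of 0.08". The list of symbols repeats 0.10 as the SD of the score and gives "detectable difference = 0.08" and "significance level for two-sided test = 1.96". The conclusion drawn is that "a sample size of around 25 children per group at 12 weeks would give 80 % power at the 0.05 significance level". The 25 is then raised to 38 per group, 76 in total, for non-response.

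The same section admits children whose BMI-for-age is more than 1 SD above the WHO reference, with no upper bound. Under Anthropometric measurement outcomes, "The primary outcome measured is the BMI-for-age z-score, which is compared between the intervention and control groups", and "children are classified into overweight (BAZ +1SD to +2SD) and obese (BAZ > +2SD) categories".

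Statistical analyses has two separate sentences on group comparison. One, beginning "The differences between intervention and control group across anthropometric measurements, pedometer step counts, whole grain and dietary intakes", uses the independent t test and the Mann–Whitney test. The next assigns the intervention effects to a repeated-measures ANCOVA, with baseline variables entered as confounders. The article states no SD of change, no residual SD and no correlation between baseline and follow-up, and it does not say which analysis the 80 % describes.

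**The concern.** The SD, the outcome and the eligibility range are all stated in the article, and they do not fit together. If 0.10 were the between-child SD of the z-score, about 95 % of the sample would lie within ±0.2 of its mean, a band about 0.4 wide. The overweight category alone is 1.0 wide, and the obese category above it is open-ended. A spread as small as 0.10 is easier to imagine for a 12-week change within a child, or for what remains after strong baseline adjustment, but the article does not call it either.

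This calculation is the only justification given for the size of the trial. If the relevant SD is larger than 0.10, power is below 80 %, and a null result could be misread as evidence that the intervention does not work.

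**Working it through.** **Inputs from the article:** SD 0.10; difference 0.08; two-sided 5 % level (1.96); 80 % power (0.84); 25 per group, planned as 38 after inflation.

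**1. Reproduce the stated figure.** n = 2 × SD² × (1.96 + 0.84)² / 0.08² = 2 × 0.01 × 7.84 / 0.0064 = 24.5, so 25 per group. Power at 25 per group is 0.807 by the normal approximation and 0.791 by the noncentral t. The arithmetic holds given the input. (The printed equation lacks the square on the sum of the Z values and would give 8.75; that is a separate matter.)

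**2. What spread does eligibility imply?** The article gives no cross-sectional SD, so these are assumptions:
- Even spread over +1 to +2 only, with no obese children: SD = 1/√12 = 0.29.
- Standard normal truncated below at +1: λ = φ(1)/[1 − Φ(1)] = 1.525; SD = √(1 + λ − λ²) = 0.446, shown as 0.45.
- A wider value, 0.60. Truncated normals with a higher mean or a larger SD give up to about 0.8.

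**3. Unadjusted comparison of z-scores**, difference 0.08. The noncentrality is 0.08 / (SD × √(2/n)), with 2n − 2 degrees of freedom:

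| SD of z-score | Power, 25 per group | Power, 38 per group |
|---|---|---|
| 0.29 | 16 % | 22 % |
| 0.45 | 9.5 % | 12 % |
| 0.60 | 7.5 % | 9 % |

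**4. Baseline-adjusted comparison.** Residual SD = SD × √(1 − r²), where r is the correlation between baseline and week 13. At 25 per group:

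| r | Residual SD (level SD 0.45) | Power | Residual SD (level SD 0.60) | Power |
|---|---|---|---|---|
| 0.90 | 0.194 | 30 % | 0.262 | 19 % |
| 0.95 | 0.139 | 51 % | 0.187 | 32 % |
| 0.97 | 0.108 | 72 % | 0.146 | 48 % |
| 0.98 | 0.089 | 88 % | 0.119 | 64 % |

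For the residual SD to equal 0.10, r = √(1 − 0.01/SD²), which is 0.975 at a level SD of 0.446 and 0.986 at 0.60.

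**5. Power by residual SD, whatever its origin:**

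| Residual SD | Power, 25 per group | Power, 38 per group |
|---|---|---|
| 0.10 | 79 % | 93 % |
| 0.15 | 46 % | 63 % |
| 0.20 | 28 % | 41 % |

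Like the article's own calculation, all of these treat children as independent observations.

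**The case against.** The strongest reply is that the plan gives the intervention effect to a repeated-measures ANCOVA with baseline covariates. The t and Mann–Whitney tests stand in another sentence, with no time point, and may be baseline or descriptive comparisons. A reader who applies the unadjusted figures to the trial might infer that the planned analysis has roughly 10 % power. The documents do not support that: the figure fits only an unadjusted comparison at an assumed SD near 0.45. Under baseline adjustment the power is undetermined and could exceed 80 %.

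A reader might also infer that an SD of 0.10 is impossible, or that it must be an SD of change. Neither follows. The value comes from an earlier study that is not at hand. It could be an SD of change, a residual SD, a standard error or a transcription slip. Implausible as labelled is as far as the text goes.

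It is also fair to say that 25 is the number left after the allowance for non-response. If fewer children are lost, power is higher: at 38 per group and level SD 0.45, it is 70 % at r = 0.95 and 89 % at r = 0.97.

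These points limit the claim about size. They do not repair the mismatch between the SD as labelled and the outcome as defined, and the correlation needed to rescue the 80 % is stated nowhere. Nor is this a detail left to an analysis plan, because the article itself states the SD, the outcome and the power.

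**Conclusion.** The point stands as a problem of input and labelling, not of arithmetic. An SD of 0.10 is implausible as the SD of the BMI z-score in a sample open to every value above +1, so the 80 % power is not established for the primary outcome as the article defines it.

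The size of the shortfall depends on quantities that the article does not give. Under the assumed level SDs of 0.29 to 0.60, an unadjusted comparison has about 7.5 % to 16 % power at 25 per group. With level SDs of 0.45 to 0.60 and correlations of 0.90 to 0.98, the baseline-adjusted analysis ranges from 19 % to 88 %. The claimed 80 % is attainable under adjustment, but only with a very high and unstated correlation.

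**What to change.** - Go back to the source study and state whether 0.10 is the SD of the level, of the change, or of a baseline-adjusted residual, with a justification. Do not relabel it as an SD of change without that check.
- Name week-13 BAZ adjusted for baseline BAZ as the primary analysis, and say that the power refers to it.
- Replace the single power figure with a range over residual SDs of 0.10, 0.15 and 0.20, at both 25 and 38 per group, as in the last table of the working.
- State that unadjusted t and Mann–Whitney tests of follow-up BAZ are descriptive and are not tests of the intervention effect.

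The cost is wording in the sample-size, outcome and statistics sections. Baseline BAZ is already measured, so no new data are needed. The downside is that the stated power becomes less favourable.
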